## Abstract

****Background**:**

Pyoderma gangrenosum (PG) is a rare inflammatory skin disorder characterised by painful and rapidly progressing skin ulceration. PG can be extremely difficult to treat and patients often require systemic immunosuppression. Recurrent lesions of PG are common, but the relative rarity of this condition means that there is a lack of published evidence regarding its treatment. A systematic review published in 2005 found no randomised controlled trials (RCTs) relating to the treatment of PG. Since this time, one small RCT has been published comparing infliximab to placebo, but none of the commonly used systemic treatments for PG have been formally assessed. The UK Dermatology Clinical Trials Network’s STOP GAP Trial has been designed to address this lack of trial evidence.

****Methods**:**

The objective is to assess whether oral ciclosporin is more effective than oral prednisolone for the treatment of PG. The trial design is a two-arm, observer-blind, parallel-group, randomised controlled trial comparing ciclosporin (4 mg/kg/day) to prednisolone (0.75 mg/kg/day). A total of 140 participants are to be recruited over a period of 4 years, from up to 50 hospitals in the UK and Eire. Primary outcome of velocity of healing at 6 weeks is assessed blinded to treatment allocation (using digital images of the ulcers). Secondary outcomes include: (i) time to healing; (ii) global assessment of improvement; (iii) PG inflammation assessment scale score; (iv) self-reported pain; (v) health-related quality of life; (vi) time to recurrence; (vii) treatment failures; (viii) adverse reactions to study medications; and (ix) cost effectiveness/utility. Patients with a clinical diagnosis of PG (excluding granulomatous PG); measurable ulceration (that is, not pustular PG); and patients aged over 18 years old who are able to give informed consent are included in the trial. Randomisation is by computer generated code using permuted blocks of randomly varying size, stratified by lesion size, and presence or absence of underlying systemic disease (for example, rheumatoid arthritis).

Patients who require topical therapy are asked to enter a parallel observational study (case series). If topical therapy fails and systemic therapy is required, participants are then considered for inclusion in the randomised trial.

****Trial registration**:**

Current controlled trials: ISRCTN35898459. Eudract No.2008-008291-14.

## **Background**

Pyoderma gangrenosum (PG) is a rare inflammatory dermatosis characterised by painful and rapidly progressive skin ulceration [1,2]. It most commonly affects the lower limbs, but can affect any other site including the peristomal area. It can be seen in association with a number of conditions including inflammatory bowel disease, rheumatoid arthritis, haematological disorders and malignancies [3-5]. It is a disease that causes considerable morbidity to patients, who often have a poor quality of life and high need for healthcare resources. Many patients require hospitalization for initial control, and regular changes of dressings by community care teams.

PG can be extremely difficult to treat and recurrent lesions are common [5]. There is a lack of published evidence regarding its treatment, largely because large-scale RCTs are difficult to conduct in a rare condition such as this. A systematic review in 2005 recommended the use of prednisolone, ciclosporin or high-dose intravenous steroids for large lesions; or potent topical steroids, tacrolimus or intralesional steroid injection for small lesions [6]. Other reviews have suggested a similar stepwise approach [7]. However, these recommendations were based on case series alone as no RCTs of these most commonly used treatments were identified and clinical guidelines are currently lacking. There has been one randomised controlled trial demonstrating superiority of infliximab over placebo [8], but such a potent drug would rarely be used as first line treatment. Many of the commonly used treatments are associated with unpleasant and potentially serious side effects, making their formal evaluation a matter of urgency. These treatments are currently being used for patients with PG without rigorous testing, or understanding of their relative efficacy, cost and side-effect profile.

In order to begin to address this lack of evidence, the first randomised controlled trial of systemic treatments for pyoderma gangrenosum is being carried out. The ‘Study of Treatments fOr Pyoderma GAngrenosum Patients’ (STOP GAP) will compare the two most commonly used systemic treatments: prednisolone and ciclosporin. The trial was granted ethics approval by the Northern and Yorkshire research ethics committee (MREC reference: 09/H0903/5), and all participants gave written informed consent. This paper is based on a summary of the current protocol (version 4.0, 30 August 2011. Further details are available on the STOP GAP Trial website at http:// http://www.stopgaptrial.co.uk) [9].

## **Methods**

### **Design**

STOP GAP is a multicentre, parallel group, observer-blind, randomised controlled trial (Figure 1). This is a superiority trial, with prednisolone as the control intervention. The decision to power the STOP GAP trial on the basis of superiority was made as (i) ciclosporin is considerably more expensive than prednisolone (which means that it would need to be considerably better than prednisolone to warrant a change in clinical practice); (ii) case series and clinical experience give the impression that ciclosporin may gain control more quickly, and have a side-effect profile that is more suitable for long-term therapy; and (iii) pragmatically, for a rare condition such as PG, this was felt to be the best approach as an equivalence trial would require a much larger trial that could only be delivered internationally, which was beyond the scope of our funding.

**Figure 1 F1:**
[figure not shown]
Flow chart of trial recruitment.

The study aims to recruit 140 patients with PG over a 4-year period. Participants are randomised using a ratio of 1:1 to receive either oral prednisolone (0.75 mg/kg/day) or oral ciclosporin (4 mg/kg/day). Patients who initially require topical therapy are asked to enter a parallel observational study, the purpose of which is to provide an estimate of treatment response to topical therapy in a well defined prospective case series, and also to enhance recruitment by allowing those who fail on topical therapy to enter the main study (Figure 1).

Follow-up is continued until the lesion has healed, or for a maximum of 6 months (whichever is sooner).

## **Objectives**

The primary objective for this trial is to assess the speed of response to treatment for the compared treatments.

Secondary objectives are to assess overall treatment response (especially time to healing), safety, and cost effectiveness of the compared treatments.

### **Participants**

Patients aged over 18 years with a clinical diagnosis of PG (as diagnosed by the recruiting dermatologist) can be enrolled into the study. There must be measurable ulceration (that is, not pustular PG) for the patient to be included. In keeping with the pragmatic nature of the study, a positive skin biopsy is not required for diagnosis since histology is rarely diagnostic, but should be performed as part of normal care in cases of diagnostic uncertainty in order to exclude alternative diagnoses. For cases where there is doubt over the clinical diagnosis, an expert panel is available to provide assistance in confirming or refuting the diagnosis.

Patients are not eligible for the study if they: (i) have granulomatous PG (which is very rare, and may respond differently to treatment); (ii) have received oral prednisolone, oral ciclosporin or intravenous immunoglobulins within 1 month prior to randomisation; or (iii) are already participating in another clinical trial. In addition patients are not eligible for the RCT arm of the study if they (i) are pregnant, lactating or at risk of pregnancy; (ii) have known hypersensitivity to either of the study drugs; (iii) have a biopsy result that is consistent with a diagnosis other than PG; (iv) have clinically significant renal impairment that would result in the investigator not normally treating with either study drug; (v) have any pretreatment investigations, the results of which would prompt the investigator not to use either study drug; (vi) have any malignant of premalignant disease where treatments might interfere with ongoing therapy or might cause harm; (vii) have any concurrent medical condition which would preclude treatment with either of the study medications; (viii) administration of a live vaccine within 2 weeks prior to randomisation; or (ix) are currently taking Rosuvastatin (Crestor) for hypercholesterolaemia, since this is contraindicated in patients taking ciclosporin.

### **Interventions**

Participants are randomised to receive either oral prednisolone 0.75 mg/kg/day or ciclosporin (Neoral) 4 mg/kg/day (in two divided doses), up to a ceiling dose of 75 mg/day prednisolone and 400 mg/day ciclosporin. The dose of study drug can be adjusted (up or down) by the investigator according to response after the week 2 visit. If possible the dose of study drug should not be altered for the first 2 weeks of the study.

The use of a double dummy design was not felt to be appropriate for this study as the side effect profile, monitoring requirements and dosing regimen for the compared drugs is very different, making such a design both costly and possibly ineffective. As a result the trial team opted to ensure blinded outcome assessment of the primary outcome (using digital images) and secure allocation concealment. Participants are prescribed study medication from standard pharmacy supplies at each recruiting hospital.

Participants of the RCT should not use any topical therapy (for example, corticosteroids or calcineurin inhibitors) after randomisation. If topical therapy has been prescribed while the participant is waiting to enter the study it should be stopped when the participant enters the RCT. All other concomitant medications should continue as per normal care. The use of live vaccines is not permitted during the intervention phase of the trial and clinicians will be advised not to start Rosuvastatin (Crestor) on any patients receiving ciclosporin as it is contraindicated. Participants are asked to assess how well they adhered to study drug at week 6 and at 6 months (or time of healing).

Participants in the observational arm of the study receive whichever topical therapy is prescribed as per normal care at the recruiting hospital (this is most likely to be clobetasol propionate (Dermovate) or tacrolimus (Protopic 0.1% or 0.03%) as there is reasonable evidence to support the use of both of these treatments [10,11].

### **Randomisation and blinding (masking)**

The randomisation schedule has been created by the Nottingham Clinical Trials Unit data manager using the ralloc Strata (College Station, TX, USA) add-on. Participants are randomised to treatment allocation using a computer-generated pseudorandom list using permuted blocks of randomly varying size between 2 and 6. Randomisation is stratified by lesion size (≥20 cm^2^ vs lesions <20 cm^2^) and presence or absence of underlying systemic disease. The randomisation schedule will be concealed until interventions are all assigned and recruitment, data collection, data cleaning and analysis are complete.

This is an observer-blind study. The primary outcome (velocity of healing) is assessed on the basis of digital images of the target lesion in order to protect against detection bias. The digital images will be assessed by two assessors who are blinded to treatment allocation, using patient number as the identifier. The images will also be used to assess global improvement in disease and the PG inflammation scale (if possible, depending on the quality of the images).

Both clinicians and participants know their treatment allocation and so no special measures are required to allow for breaking of treatment codes. However, treatment allocation will not be revealed to the recruiting physician until participants’ details and key stratification variables have been irrevocably entered by the physician onto the web-based randomisation site.

### **Primary outcome**

The primary outcome is velocity of healing at 6 weeks. This will be captured for a single target lesion per patient and measured using digital photography and Verge Videometry VEV MD (Vista Medical, Winnipeg, Canada) computerised planimetry [12]. If multiple lesions are present, the target lesion should be the lesion that is most able to be photographed on a single plane (that is, not around the curvature of a limb). Digital images will be taken at baseline, 6 weeks and when the ulcer has healed (maximum 6 months). In addition, maximum longitudinal length and maximum perpendicular length will be measured in order to provide some measure of improvement in case of difficulties with the digital images, or if the lesion extends around the curvature of a limb. This will be converted to approximate area by the formula: length × width × 0.785, which approximates to an ellipse for the purpose of randomisation and analysis.

Velocity of healing at 6 weeks was chosen as the primary outcome as it is unlikely to be compromised by the single blind nature of the study, and does not require lengthy follow-up, thus minimising the possibility of missing data. Previous work in patients with venous leg ulcers suggests that velocity of healing is a good surrogate for subsequent healing [13].

### **Secondary outcomes**

Secondary outcomes include the following: (1) time to healing assessed by participants (estimated to the nearest week) based on the time at which sterile dressings are no longer required for the wound. Healing is confirmed by the clinician, and documented using digital photography at the first opportunity. Time to healing is important clinically as it will be used to confirm the primary outcome as a useful surrogate measure. It also gives an indication of duration of treatment, which therefore provides information on cumulative drug toxicity. (2) PG specific global assessment of efficacy (derived from a study by Foss *et al.*[14]) as assessed by the clinician and the patient at 2 weeks, 6 weeks and at 6 months (or healed). This will also be assessed on the digital images by an independent assessor. (3) Inflammation assessment scale. This is a combination scale including erythema, border elevation and exudate (based on a scale reported by Foss *et al.*[14]). The inflammation assessment scale is recorded by the clinician and the participant at baseline, 2 weeks, 6 weeks and when the ulcer has healed (maximum 6 months). This will also be assessed on the digital images by an independent assessor. (4) Self-reported pain. Each day for the first 6 weeks of the trial participants report the severity of the pain in a study diary (none, mild, moderate, severe or extreme), and whether or not painkillers were taken. (5) Health-related quality of life assessed at baseline, 6 weeks and 6 months (or healed), using validated questionnaires: Dermatology Life Quality Index [15] and the EQ-5day [16]. (6) Time to recurrence assessed at the end of the trial. A recurrence is defined as the occurrence of a further episode of PG (at any site) that appears after the target lesion has been confirmed as being healed by a physician (or nurse). Self-reported healing that has not been confirmed by a medical professional, and which subsequently recurs, will not be classed as a recurrence and handled as a continuation of the initial episode. (7) Number of treatment failures. Treatment failures are defined as being participants who withdraw (or are withdrawn) from their randomized treatment because of treatment intolerance or worsening of the PG, or those who continue to have any unhealed ulcers after 6 months of follow-up. (8) Adverse reactions to study medications. Adverse events that are classed as possibly, probably or definitely relating to the study medication. (9) Cost effectiveness of the compared treatments.

For participants in the observational study, only efficacy outcomes are being collected (no safety or cost-effectiveness outcomes will be reported).

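### Healing is called by an unblinded participant and clinician; a blinded closed/not-closed reading of a photograph already taken would check the event at little cost

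*Protocol article*

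**What the plan says.** All references are to the protocol article.

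- **Who calls healing (Secondary outcomes, item 1).** For the ulcer, the outcome is defined as follows: "time to healing assessed by participants (estimated to the nearest week) based on the time at which sterile dressings are no longer required for the" […]. The item adds: "Healing is confirmed by the clinician, and documented using digital photography at the first opportunity".
- **Who is blinded (Randomisation and blinding).** "Both clinicians and participants know their treatment allocation". For the images: "The digital images will be assessed by two assessors who are blinded to treatment allocation, using patient number as the identifier".
- **What the images are for (same section).** Besides the primary outcome: "The images will also be used to assess global improvement in disease and the PG inflammation scale". This comes with a proviso about adequate image quality. Under Secondary outcomes, items 2 (global assessment) and 3 (inflammation scale) each add a reading of the images by an independent assessor. Item 1 does not.
- **When images are taken (Primary outcome).** "Digital images will be taken at baseline, 6 weeks and when the ulcer has healed (maximum 6 months").
- **Standing of the outcome.** Under Objectives: "Secondary objectives are to assess overall treatment response (especially time to healing"), together with safety and cost effectiveness. Item 1 adds that time to healing will serve to support the primary outcome as a surrogate. Under Statistical analysis, the arms are compared on it by adjusted Cox regression.

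**The concern.** Whether an ulcer still needs a sterile dressing is a judgement. The participant makes it and the clinician confirms it, both knowing the treatment. Expectation could also have a direction, because the Design section records an impression that ciclosporin may work faster.

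The trial team saw this hazard for the primary outcome. It chose one that the open design was unlikely to compromise and had it read blind from images. The healing call has no such check, although the image exists and blinded readers are in place.

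A healing call also has consequences beyond the Cox model. It contributes to cost per healed ulcer at 6 months, and it ends follow-up (Design section), so an ulcer called healed too soon may not be photographed again. The healing photograph may then be the only objective record of whether the call was right.

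**Working it through.** **1. Is this a stated choice or only condensation?** The three items side by side:

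| Secondary outcome | Unblinded assessment | Independent image reading stated |
|---|---|---|
| 1 Time to healing | participant, confirmed by clinician | no (photograph documents healing) |
| 2 Global assessment | clinician and patient | yes |
| 3 Inflammation scale | clinician and participant | yes |

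The Interventions section likewise describes blinded assessment as a protection for the primary outcome. The article had room to state the reading for two outcomes and did not state it for the first, so the gap is in the text.

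**2. The plan's own figure.** The point rests on no figure in the article, but the illustration below uses its evaluable sample size. Per arm, n = 2(1.960 + 0.842)² / 0.5² = 62.8, rounded up to 63. In total that is 126, and 126 / 0.90 = 140, which agrees with the Sample size section. Adding an image reading does not change this.

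**3. Illustration of false healing calls.** The documents give neither a healing rate nor a miscalling rate, so these inputs are assumed: 63 per arm, no true difference, exponential healing times rounded up to whole weeks, and 50% or 70% healed by 26 weeks. The weekly rate is −ln(1 − p)/26, that is 0.0267 or 0.0463. In one arm only, a fraction f of the ulcers unhealed at 26 weeks is given a random healing week from 1 to 26. Each case has 2,000 simulated trials. The test is an unadjusted log-rank test at two-sided 5%, and the hazard ratio is exp[(O − E)/V], averaged on the log scale.

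| Healed by 26 weeks | f | Expected false calls, 63 × (1 − p) × f | Apparent HR | False-positive rate |
|---|---|---|---|---|
| 50% | 0 | 0 | 1.01 | 5.8% |
| 50% | 10% | 3.2 | 1.15 | 8% |
| 50% | 20% | 6.3 | 1.31 | 20% |
| 70% | 0 | 0 | 0.99 | 5.5% |
| 70% | 10% | 1.9 | 1.07 | 6% |
| 70% | 20% | 3.8 | 1.16 | 12% |

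So about 2 to 6 wrong calls, all in one arm, produce an apparent hazard ratio of 1.07 to 1.31.

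**4. Early dating is a separate matter.** In the same set-up, dating healing 1 or 2 weeks early in one arm gives hazard ratios of 1.05 to 1.14 and false-positive rates of 6% to 9%. With a 2-week lag and a 12-week exponential median, the hazard ratios are 1.08 and 1.16. An image taken at the first opportunity after healing can show whether the ulcer is closed but not in which week it closed. An ulcer called early that has closed by the time of the photograph would be read as closed. These hazard ratios therefore do not measure what an image reading removes.

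**The case against.** The strongest reply is that this is a disclosed and partly mitigated design choice. The article explains why a double dummy was rejected and why blinding was concentrated on the primary outcome. A second person must confirm healing, and self-reported healing that is unconfirmed and then breaks down is counted as the same episode. Item 2 already foresees an independent image reading at the healed timepoint. The definition, when dressings can stop, is partly a care decision that no photograph settles. The full protocol may say more.

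Much of this stands:

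- The article does not contradict itself, and the definition need not be replaced.
- The independent reading in item 2 is not used to check the healing event, and the article does not show whether its scale has a closed category.
- Confirmation by the clinician is a safeguard, but an unblinded one.

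A reader might also infer more than the documents support:

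- **That image-confirmed healing should replace the event for healing, recurrence, failure and cost alike.** Treatment failure also covers withdrawal for intolerance or worsening, and any unhealed ulcer. A reading of one target lesion cannot decide it. After an overturned call no later image is scheduled, so the true healing date would be unknown.
- **That the surrogate check is undermined.** A shift between arms does not by itself destroy the association, within patients, between early velocity and healing time.
- **That the primary outcome is affected.** It keeps its blinded image reading, except where clinician measurements stand in for missing images.
- **That bias is present.** Nothing in the documents shows that either arm's ulcers would be miscalled, let alone 20% of them.

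**Conclusion.** The point holds as a cheap improvement, not as an error. The outcome singled out among the secondary objectives rests on an event decided and confirmed by people who know the allocation. A blinded check is available and is specified for two other secondary outcomes but not for this one.

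The size cannot be estimated from the documents. The hazard ratio of about 1.07 to 1.31 assumes no true difference, 50% or 70% healing by 26 weeks, and 10% to 20% of unhealed ulcers called healed in one arm only. If miscalling is rare or equal in both arms, the distortion will be smaller. What the check can detect is false healing calls; any bias in the reported week remains.

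**What to change.** **Reading.** Under Randomisation and blinding and under Secondary outcomes item 1, have the existing blinded assessors record closed, not closed or unreadable for the target lesion on the healed (or 6-month) image.

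**Reporting.** Keep the participant-reported, clinician-confirmed definition for the planned analysis. Show by arm how often the blinded reading agrees with it.

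**Added analysis, specified in advance.** Analyse time to healing, and target-lesion healing by 6 months (which feeds cost per healed ulcer), counting only image-confirmed healing as the event.

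- Keep the participant-reported week as the date of confirmed events.
- Treat overturned calls as not healed, handled in two ways: censored at the image date, and carried as unhealed to 6 months.
- Where the image is missing or unreadable, use the clinician's confirmation.

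**Scope.** Do not apply the reading to the treatment-failure definition.

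**Cost.** One extra item per image, with no new visit, image, reader or patients. Some images will be unreadable. Because follow-up ends at healing, an overturned call will have no later image to date true closure, which is why both handlings are needed.

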### **Statistical analysis**

The primary analysis will be according to the intention to treat principle, and will adjust for known prognostic baseline covariates. There are no formal planned interim analyses, but progress reports on all data issues are presented to a Data Monitoring Committee (DMC).

The primary outcome is to be assessed at 6 weeks, which reduces the likelihood of having missing data for this outcome. If digital images are not available for any participants, then the physical length and width measurements recorded by the clinician will be used in place of the computer generated planimetry measurements. If neither a digital image, nor physical measurements are available at 6 weeks, multiple imputation will be used using the assumption that the data are missing at random.

All primary outcome data will be double data entered and 10% of other data will be entered twice and checked for errors.

Categorical variables will be summarised with the number and proportion of participants falling in each category. Continuous variables will be summarised using the number available, number missing, mean and standard deviation (SD), or median, 25th and 75th quartiles, and minimum and maximum values as appropriate.

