## **Discussion**

The STOP GAP trial is a unique study that could not be achieved without the collaborative efforts of large numbers of participating dermatologists, nurses, NHS Trusts and research networks. Recruitment is taking place at approximately 50 UK (and Ireland) secondary care dermatology departments, all of whom are contributing just 1 or 2 participants per year. Investigators are contributing on a voluntary basis because they believe that this is an important clinical question that will help to inform their clinical practice. Such a recruitment model means that it is not possible to provide dedicated STOP GAP research nurses at individual sites, and that the recruiting dermatologists are sometimes isolated. However, the development of the National Institute for Health Research (NIHR) Clinical Research infrastructure in the England (and CRC Cymru in Wales) means that support is now available to deliver collaborative trials of this kind, and many nurses are available within participating NHS Trusts to assist with patient recruitment and follow-up.

As a model for conducting trials of rare skin conditions, the STOP GAP trial is methodologically interesting in that efforts have been made to include all PG patients who are willing to take part, by inclusion in either the RCT or the observational study. This means that the trial will not only deliver the largest RCT ever to have been conducted in PG patients, but also the largest prospective case series of patients treated with topical therapy.

The use of a parallel observational study alongside the RCT also has advantages for recruitment as it means that patients with mild disease, who are initially considered to be ineligible for the main RCT, remain in contact with the trial team. If topical treatment fails and systemic therapy is indicated, these patients can then be considered for inclusion in the RCT. This approach is particularly useful for rare conditions, where few patients are seen at recruiting centres and the evidence- base for treatment is poor (making a prospective case series more valuable).

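### Treatment failure, as defined, leaves out a participant withdrawn for a static ulcer who then heals on other treatment by 6 months

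*Protocol article*

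**What the plan says.** The protocol article (Methods, Secondary outcomes, item 7) lists the number of treatment failures as an outcome. It gives two limbs. The first covers participants who "withdraw (or are withdrawn) from their randomized treatment because of treatment intolerance or worsening of the PG". The second adds "or those who continue to have any unhealed ulcers after 6 months of follow-up". The item is worded as a definition, not as a list of examples, and nothing elsewhere in the article adds lack of response or a change of drug.

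Three other statements bear on it:
- Design: "Follow-up is continued until the lesion has healed, or for a maximum of 6 months (whichever is sooner").
- Interventions: "The dose of study drug can be adjusted (up or down) by the investigator according to response after the week 2 visit". No rule on changing drug is stated.
- Randomisation and blinding: "Both clinicians and participants know their treatment allocation".

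**The concern.** An outcome that counts failures of a drug should include the participant whose drug was stopped because it did not work. Item (7) does so if the ulcer got worse, or if it is still open at 6 months. It does not do so if the ulcer simply failed to improve and later healed on something else. That participant is then credited to the randomised drug as a non-failure.

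Two things are at stake. First, the failure count in each arm may be too low. Second, for a participant who changes treatment and heals, the classification depends on the reason written down for stopping. That reason is chosen by someone who knows the allocation, and the blinded reading of images does not protect it.

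**Working it through.** **Figures in the plan.** No expected failure rate or withdrawal rate is given for this outcome. The only related figure is the total of 140, which is set for the primary outcome (Sample size: 0.5 SD, two-sided 5%, 80% power, about 10% loss).
- Normal approximation: 2 × (1.960 + 0.842)² / 0.5² = 62.8, so 63 per arm and 126 in total. 126 / 0.90 = 140, as stated.
- Exact t test: 64 per arm and 128 in total. 128 / 0.90 = 142.2, so 143. Equally, 140 falls to 128 with a loss of 12/140 = 8.6%, which fits the stated approximate allowance.

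The failure outcome does not enter this calculation, so N is untouched.

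**The definition applied as a rule.** Consider four participants, each of whom stops the randomised drug and receives other treatment:

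| Reason for stopping | All ulcers healed by 6 months? | Withdrawal limb met? | Unhealed limb met? | Counted as failure? |
|---|---|---|---|---|
| Intolerance | Yes | Yes | No | Yes |
| Worsening | Yes | Yes | No | Yes |
| Static ulcer | No | No | Yes | Yes |
| Static ulcer | Yes | No | No | **No** |

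Only the last row escapes. The first two rows show that later healing on other treatment does not normally cancel a failure. In the last row it does, and no reason is given for the difference.

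**Size, under assumed rates.** Let *m* be the share of an arm in the last row, with 140/2 = 70 per arm.
- Missed participants = 70 × *m*. For *m* = 5%, 10% and 15% this gives 3.5, 7 and 10.5.
- If 5% to 20% of an arm stop for non-response and half of them then heal, *m* = 0.5 × 5% to 0.5 × 20% = 2.5% to 10%.

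**Effect on the comparison.** Let *D* be the true difference in failure rates, arm A minus arm B. The counted difference is *D* − (*m*A − *m*B).
- Equal shares: with a true rate of 40% in both arms and *m* = 10% in both, the counted rates are 30% and 30%. The difference is unchanged, but 7 of 70 are missed in each arm.
- Unequal shares, equal true rates: with 40% in both arms and *m* = 5% and 15%, the counted rates are 35% and 25%. A 10-point difference is created.
- Unequal shares, A truly worse: if 15% and 5% stop for non-response and half heal, *m* = 7.5% and 2.5%, so the counted difference is *D* − 5 points. With the shares reversed it is *D* + 5 points.

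All these rates are assumptions, and the direction depends on them.

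**The case against.** The strongest reply is that the gap is narrow. The ulcer must be static and not worse, the drug must be stopped for that reason, and every ulcer must have healed by 6 months. Non-responders who do not heal are caught by the second limb. The article describes PG as rapidly progressive, so some uncontrolled disease would count as worsening anyway. Early non-response is also captured elsewhere, by planimetry at 6 weeks and by the global assessment at 2 and 6 weeks. All of this stands and limits the importance of the point. It does not remove the inconsistency in the rule.

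It could also be said that healing after a change of drug properly belongs to the allocated arm, since "The primary analysis will be according to the intention to treat principle". That sentence concerns the primary analysis. Item (7) does not follow a strategy view either, because it counts intolerance or worsening as failure whatever happens later.

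The full protocol (version 4.0) is not shown and may define failure more broadly. That is possible, but the article states a closed definition, so at the least the two should agree.

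A reader might infer more than the text supports:
- *That non-response is the commonest reason for stopping.* The article gives no such figure. The only response-driven change it describes is dose adjustment, and it neither describes nor excludes a change of systemic drug.
- *That participants who have a second systemic agent added are also missed.* The sentence "All other concomitant medications should continue as per normal care" is about continuing existing medication and does not show that new PG treatment may be added.
- *That the weaker drug is made to look better.* The arithmetic shows that the direction depends on unknown shares.
- *That starting any other systemic treatment should itself count as failure.* In patients with associated bowel disease or rheumatoid arthritis, attributing such treatment to PG may be difficult, and an unblinded prescribing decision would then trigger the outcome.

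**Conclusion.** The point holds for one defined group: participants withdrawn for lack of response without worsening, whose ulcers have all healed by 6 months. For them the stated rule gives a result at odds with its treatment of intolerance and worsening, undercounts failures of the randomised drug, and leaves the classification open to an unblinded choice of reason. This is a rule that the article states, not a detail it leaves out.

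How many participants are affected cannot be derived from the article. Under assumed shares of 5% to 15% it would be 3.5 to 10.5 of 70 in an arm. Whether the between-arm difference is unchanged, reduced or created is unknown. This is one of nine secondary outcomes, and the primary outcome and sample size are not affected. The definition should be corrected, but the trial's main conclusion does not depend on it.

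**What to change.** Reword item (7) so that treatment failure means stopping the randomised treatment because of intolerance, worsening, or lack of response of the PG, or having any ulcer unhealed at 6 months. Record the reason for withdrawal in set categories, with worsening and lack of response as separate entries. Both then lead to the same classification, so the choice between them no longer decides failure status. If the full protocol already counts lack of response, align the article's wording with it.

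This changes only how participants are counted. It says nothing about when treatment may be changed.

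The cost is one revised sentence and a fixed list of reasons. The existing definition already requires the reason for withdrawal to be known. There are two small downsides: the reported failure rate can rise, and lack of response remains a clinician's judgement.
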